## 10 PHARMACOVIGILANCE

### 10.1 Terms and Definitions

#### 10.1.1 Medicines for Human Use (Clinical Trials) Regulations 2004 (SI 2004/1031) Definitions

As the insulin analogues are classed as investigational medicinal products (IMPs) in this trial, pharmacovigilance for SCIPi is subject to the following Medicines for Human Use (Clinical Trials) Regulations 2004 (SI 2004/1031) definitions:

##### **Adverse Event (AE)**

Any untoward medical occurrence in a subject to whom a medicinal product has been administered, including occurrences which are not necessarily caused by or related to that product.

##### **Adverse Reaction (AR)**

Any untoward and unintended response in a subject to an investigational medicinal product which is related to any dose administered to that subject.

##### **Unexpected Adverse Reaction (UAR)**

An adverse reaction the nature and severity of which is not consistent with the information about the medicinal product in question set out in:

- In the case of a product with a marketing authorization, in the summary of product characteristics for that product
- In the case of any other investigational medicinal product, in the investigator's brochure relating to the trial in question.

##### **Serious Adverse Event (SAE), Serious Adverse Reaction (SAR) or Suspected Unexpected Serious Adverse Reaction (SUSAR)**

Any adverse event, adverse reaction or unexpected adverse reaction, respectively, that:

- results in death
- is life-threatening\* (subject at immediate risk of death)
- requires in-patient hospitalisation or prolongation of existing hospitalisation\*\*
- results in persistent or significant disability or incapacity, or
- consists of a congenital anomaly or birth defect
- Other important medical events

\*'life-threatening' in the definition of 'serious' refers to an event in which the patient was at risk of death at the time of the event; it does not refer to an event which hypothetically might have caused death if it were more severe.

\*\*Hospitalisation is defined as an inpatient admission, regardless of length of stay, even if the hospitalisation is a precautionary measure for continued observation. Hospitalisations for a pre-existing condition, including elective procedures that have not worsened, do not constitute an SAE.

\*\*\*Other important medical events that may not result in death, be life-threatening, or require hospitalisation may be considered a serious adverse event/experience when, based upon appropriate medical judgment, they may jeopardise the subject and may require medical or surgical intervention to prevent one of the outcomes listed in this definition.

### 10.1.2 National Research Ethics Service (NRES) Definitions

As SCIPi involves medical devices, safety reporting for the trial is subject to the following NRES safety reporting definitions for related and unexpected SAEs:

- **'related'** – that is, it resulted from administration of the medical device or any of the research procedures;
- **'unexpected'** – that is, the type of event is not listed in the protocol as an expected occurrence.

NRES require that a SAE occurring to a research participant, where in the opinion of the Chief Investigator the event is related and unexpected (RUSAE), is reported to the main Research Ethics Committee (REC).

### 10.1.3 Medicines and Healthcare products Regulatory Agency (MHRA) Adverse Incident Centre (AIC) Definitions

As the trial involves the use of CE-marked medical devices employed for their intended purpose, adverse incidents are also reportable to the Medicines and Healthcare products Regulatory Agency (MHRA) Adverse Incident Centre (AIC) under the User Devices Vigilance requirement.

The MHRA AIC define an **Adverse Incident (AI)** as:

- An event that causes, or has the potential to cause, **unexpected or unwanted effects** involving the safety of device users (including participants) or other persons.

Causes of AIs involving devices may include:

- Design or manufacturing problems;
- Inadequate servicing and maintenance;
- Inappropriate local modifications;
- Unsuitable storage and use conditions;
- Selection of the incorrect device for the purpose;
- Inappropriate management procedures;
- Poor user instructions or training (which may result in incorrect user practice).

Conditions of use e.g. environmental conditions or location may also give rise to adverse incidents.

Any adverse incident involving a device or its instructions for use should be reported to the MHRA AIC, especially if the incident has led to or, were it to occur again, could lead to all occurrences listed under SAEs in section 10.1.1 above, as well as:

- Unreliable test results and associated risk of mis-diagnosis or inappropriate treatment;
- Ongoing faults that successive service/maintenance visits have failed to rectify.

The MHRA AIC also request that minor safety or quality problems with the device should also be reported as these can help demonstrate trends or highlight inadequate manufacturing or supply systems. Reports of adverse incidents that appear to be caused by human error should also be reported because:

- The error may be partly (or wholly) due to deficiencies in the design of the device or instructions for use;
- They may prompt promulgation of advice or device design improvements that will help prevent repetition of mistakes.

By these definitions AIs are the same as related and unexpected AEs and related and unexpected SAEs.

## 10.2 Severity / Grading of Adverse Events

The assignment of the severity/grading should be made by the investigator responsible for the care of the participant using the definitions below.

Regardless of the classification of an AE as serious or not, its severity must be assessed according to medical criteria alone using the following categories:

**Mild:** does not interfere with routine activities

**Moderate:** interferes with routine activities

**Severe:** impossible to perform routine activities

A distinction is drawn between serious and severe AEs. Severity is a measure of intensity (see above) whereas seriousness is defined using the criteria in section 10.1.1, hence, a severe AE need not necessarily be a Serious AE.

## 10.3 Relationship to disease under study

Participants for this study will be monitored for adverse events and serious adverse events related to the disease under study. The assignment of causality should be made by the investigator responsible for the care of the participant. These events should be recorded on the related adverse events form and related serious event forms.

## 10.4 Relationship to Trial Treatment

Participants for this study will be monitored for adverse events and serious adverse events related to the trial treatment. The assignment of the causality should be made by the investigator responsible for the care of the participant using the definitions in table 2.

If any doubt about the causality exists the local investigator should inform the MC-CTU who will notify the Chief Investigator. In the case of discrepant views on causality between the investigators, the MHRA, NRES and MHRA AIC will be informed of both points of view.

**Table 2: Definitions of Causality**

| Relationship            | Description                                                                                                                                                                                                                                                                                                           |
|-------------------------|-----------------------------------------------------------------------------------------------------------------------------------------------------------------------------------------------------------------------------------------------------------------------------------------------------------------------|
| Unrelated        | There is no evidence of any causal relationship.
There is an alternative cause for the AE.                                                                                                                                                                                                                         |
| Unlikely         | There is little evidence to suggest there is a causal relationship (e.g. the event did not occur within a reasonable time after administration of the trial intervention). There is another reasonable explanation for the event (e.g. the participant's clinical condition, other concomitant treatment).            |
| Possibly         | There is some evidence to suggest a causal relationship (e.g. because the event occurs within a reasonable time after administration of the trial intervention). However, the influence of other factors may have contributed to the event (e.g. the participant's clinical condition, other concomitant treatments). |
| Probably         | There is evidence to suggest a causal relationship and the influence of other factors is unlikely.                                                                                                                                                                                                                    |
| Almost certainly | There is clear evidence to suggest a causal relationship and other possible contributing factors can be ruled out.                                                                                                                                                                                                    |

\*Possibly, probably, or almost certainly related will be referred to throughout the protocol as 'related'.

## 10.5 Expectedness

### **Insulin analogue:**

An AE whose causal relationship to the insulin is assessed by the investigator as “possible”, “probable”, or “definite” is an Adverse Drug Reaction. Refer to the relevant SPC for a list of expected adverse reactions. All events judged by the investigator to be possibly, probably, or almost certainly related to the insulin analogues, graded as serious (see section 10.1.1) and **unexpected** should be reported as a SUSAR.

### **Device:**

An AE whose causal relationship to the device is assessed by the investigator as “possible”, “probable”, or “definite” is a Related Adverse Event. Refer to the relevant manufacturer’s instructions for use for list of expected related adverse events. All events judged by the investigator to be possibly, probably, or almost certainly related to the devices, graded as serious (see section 10.1.1) and **unexpected** should be reported as a Related Unexpected SAE.

## 10.6 Reporting Procedures

### **Non serious ARs/AEs**

ARs/AEs will only be reported for participants where consent has been obtained and the causal relationship has been assessed and judged by the investigator to be related to the trial treatment (see section 10.4) and / or disease under study (type 1 diabetes), which occurs from the start of randomised treatment until final follow-up visit at 12 months post-diagnosis. The events should be recorded on a Related Adverse Event Form, which should be transmitted to the MC-CTU within seven days of the clinical research team becoming aware of the event.

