#### Secondary Endpoint(s)

- a. Percentage of participants in each group with HbA1c <6.5%
- b. Incidence of severe hypoglycaemia
- c. Incidence of diabetic ketoacidosis
- d. Change in BMI SDS
- e. Height
- f. Insulin requirements (units / kg /day)
- g. PedsQL
- h. Incremental cost per QALY gained
- i. Partial remission

On or near completion of the 12 month study permission will be sought from participants and their carers for ongoing submission of routine clinical data to the research team for a further nine years to enable long term outcomes to be reported. This will include:

- a. HbA1c;
- b. Insulin treatment regimen;
- c. BMI;
- d. Insulin dose (units/kg/day);
- e. Serious adverse events;
- f. Complications of T1DM.

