### **8.1 Schedule for Follow-up**

The study duration of each participant (including follow-up period) is one year from the date of randomisation. All participants will be reviewed at the diabetes outpatient clinic every three months as per standard clinical practice and will have four follow up visits at 3-, 6-, 9- and 12- months from randomisation. Participants will have a flexible window of  $\pm 15$  days to report for each follow up visit.

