## **8.3 Procedures for Assessing Safety**

### **8.3.1 Adverse events:**

Participants will be monitored for treatment related adverse events (AEs) and treatment related serious adverse events (SAEs) (see section 10 for details). They will be issued with a diary to document home episodes of severe hypoglycaemia and diabetic ketoacidosis. Treatment diaries and telephone logs will be assessed at each study visit for any treatment related AEs and related SAEs.

For this study we will also monitor adverse events related to the disease under study.

In addition to self-reporting, local hospital databases will be interrogated at each clinical assessment to ascertain whether the subject has been treated for a related SAE in the preceding three months. Related AEs (including incidences of severe hypoglycaemia and diabetic ketoacidosis) and related SAEs will be reported as described in section 10.6.

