## **9.6 Analysis Plan**

The trial will be analysed and reported using the 'Consolidated Standard of Reporting Trials' (CONSORT) and the International Conference on Harmonisation E9 guidelines. A full and detailed statistical analysis plan will be developed prior any comparative analysis of the trial data. The main features of the statistical analysis plan are included here.

A p-value of 0.05 or less will be used to declare statistical significance for all analyses. Rather than adjust for multiplicity relevant results from other studies already reported in the literature will be taken into account in the interpretation of results.

Primary analysis will be the intention to treat principle, a secondary analysis will be conducted using the per protocol approach. The purpose of the per protocol approach is to consider the robustness of the conclusions reached from the analysis using the intention to treat principle to protocol deviations.

The primary outcome HbA1c will be compared between the trial groups using a two group t-test. Difference in means with 95% confidence intervals will be presented. Analysis of covariance will be used to adjust for baseline values (excluding HbA1c measured at baseline) and important prognostic factors.

Missing data will be monitored and strategies developed to minimise its occurrence, however as much data as possible will be collected about the reasons for missing data and this will be used to inform the handling of missing data.

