### Serious ARs/AEs/SUSARs/RUSAEs

SARs, SAEs, SUSARs and RUSAEs will only be reported for participants where consent has been obtained and the causal relationship has been assessed and judged by the investigator to be related to the trial treatment (see section 10.4) and / or disease under study (see section 10.3), which occurs from the start of randomised treatment until final follow-up visit at 12 months post-diagnosis. They should be reported to the MC-CTU using the related SAE form **within 24 hours** of the local site becoming aware of the event.

The related SAE form asks for the nature of event, date of onset, severity, corrective therapies given, outcome and causality. The responsible investigator should sign the causality of the event. Additional information should be sent within 5 days if the reaction/event has not resolved at the time of reporting.

Refer to section 10.9 and 10.10 for further details on the reporting procedures and the responsibilities of the investigators and the MC-CTU respectively. Any questions concerning adverse event reporting should be directed to the MC-CTU in the first instance. A flowchart is given below to aid in determining reporting requirements.

**All hospital admissions** will be reported as part of the routine baseline and follow-up CRFs and using electronic databases. Only report hospital admissions using the related SAE CRF if they occur in the specified time frame and are judged to be related to the trial treatment.

**All deaths** that occur between the time of consent and the 12 month follow-up should be reported to the MC-CTU using the death CRF **within 7 days** of the clinical research team becoming aware of the event. If a patient's death has been assessed and judged by the investigator to be related to the trial treatment (see section 10.4), a related SAE CRF should also be completed.

[figure not shown]

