### 11.2 Ethical Approval

The trial protocol, including the Parent/Patient Information Sheets and Consent/Assent forms and all other relevant study documentation has received the favourable opinion of the North West 3 REC - Liverpool East Multi-centre Research Ethics Committee (MREC). All participating centres must be granted NHS permission by their Local Research & Development (R&D) department prior to commencing recruitment. A copy of local R & D approval and the Parent/Patient Information and Consent/Assent form on local headed paper should be forwarded to MC-CTU before the site is initiated and patients recruited.

Proxy consent from the parent or legally acceptable representative should be obtained prior to each patient participating in the trial, after a full explanation has been given of the treatment options, including the conventional and generally accepted methods of treatment. Age and stage-of development specific Patient Information and Consent Forms (PISC) should also be implemented and patient assent obtained where appropriate. The right of the parent/ legal representative to refuse consent for the minor to participate in the trial without

giving reasons must be respected. After the patient has entered the trial, the clinician must remain free to give alternative treatment to that specified in the protocol, at any stage, if he/she feels it to be in the best interest of the patient. However, the reason for doing so should be recorded and the participant will remain within the trial for the purpose of follow-up and data analysis. Similarly, the parent/legal representative of the participant remains free to withdraw the participant at any time from the protocol treatment and trial follow-up without giving reasons and without prejudicing the further treatment of the minor.

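### Section 10.6 starts reporting of severe hypoglycaemia and ketoacidosis when the allocated treatment starts, not at randomisation, so treatment received sets the start of two safety endpoints

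*Protocol*

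**What the plan says.** Protocol section 4.2 lists "Incidence of severe hypoglycaemia" and "Incidence of diabetic ketoacidosis" as secondary endpoints and gives neither its own start date. Section 8.3.1 sets the route: "Related AEs (including incidences of severe hypoglycaemia and diabetic ketoacidosis) and related SAEs will be reported as described in section 10.6". In section 10.6 the part on non-serious events limits reporting to a related event "which occurs from the start of randomised treatment until final follow-up visit at 12 months post-diagnosis", and the part on serious events repeats the same window.

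Other sections use a different origin or none:
- **8.1:** "The study duration of each participant (including follow-up period) is one year from the date of randomisation".
- **9.6:** "Primary analysis will be the intention to treat principle".
- **11.2:** where a clinician gives something other than the protocol treatment, "the participant will remain within the trial for the purpose of follow-up and data analysis".
- **10.6, deaths:** all deaths "that occur between the time of consent and the 12 month follow-up should be reported to the MC-CTU".
- **10.3 and 10.9:** disease-related events go on the related-event forms, and the investigator reports related events seen during the study. Neither section mentions the start of treatment.

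**The concern.** A window that opens at first treatment can suit the attribution of reactions to a product. It does not suit a randomised comparison of incidence, where every randomised child should be counted from the same origin.

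Here the opening depends on what happens after allocation. Section 7.2 trains all participants on injections and gives the CSII arm pump training as well, so the allocated treatment may begin later in that arm. A child who never begins it has no opening date at all. If sites follow 10.6 literally, the arms could contribute different observation time to the two endpoints, and non-starters could drop out of the event count while staying in the intention-to-treat denominator. The first days after diagnosis would be the part least consistently recorded.

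The same sentence closes the window by reference to diagnosis. That is a separate matter and is not pursued here.

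**Working it through.** The protocol states no figure on this point that could be reproduced; its sample-size calculation concerns HbA1c and is not involved. The check has a textual part and a sizing part.

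**1. Tracing the rule.** 4.2 gives no start date → 8.3.1 refers both endpoints to 10.6 → both parts of 10.6 open at the start of the allocated treatment. Under 10.6 a hospital admission outside that window stays off the related SAE form and appears only on routine forms. An episode treated at home has the diary but no admission record.

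**2. Inputs for sizing.**
- Latest intended start of treatment: 14 days from diagnosis, the same limit in both arms (7.1).
- Follow-up: one year from randomisation (8.1), taken as 365 days.
- Group size: 158 (9.4).
- Assumed, because the protocol does not give them: *g*, the days from randomisation to treatment start; *k*, the event rate in the gap relative to later; *m*, the proportion of an arm that never starts.

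**3. Share of a year's events falling in the gap.** Share = gk / (gk + 365 − g).

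| g (days) | k | Calculation | Share |
|---|---|---|---|
| 3 | 1 | 3/365 | 0.8% |
| 7 | 1 | 7/365 | 1.9% |
| 14 | 1 | 14/365 | 3.8% |
| 14 | 2 | 28/379 | 7.4% |
| 14 | 5 | 70/421 | 16.6% |

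**4. Effect on the comparison in the extreme case.** Suppose the 14-day gap occurs in one arm only, no gap event is recovered by another route, and the denominators run from randomisation. A true rate ratio of 1 then appears as 351/365 = 0.96 (k = 1), 351/379 = 0.93 (k = 2) or 351/421 = 0.83 (k = 5). If person-time also began at treatment start, the k = 1 distortion would vanish, but the two arms would then be compared over different periods after diagnosis.

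**5. Non-starters.** Suppose a proportion m of one arm never starts, has the same event rate as the rest, stays in the denominator, and has no events reported. The ratio is then 1 − m.
- m = 1% (158 × 0.01 = 1.6 children): 0.99.
- m = 5% (7.9 children): 0.95.
- m = 10% (15.8 children): 0.90.

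Combined with a 14-day gap at a constant rate, (1 − m) × 351/365 gives 0.95, 0.91 and 0.87 (0.865 before rounding).

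**6. After the change.** With the window opened at randomisation, g = 0, so the share missed is 0 and non-starters return to the count. The sample size does not change.

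**The case against.** The strongest reply is that 10.6 is not the only text and the related-event forms are not the only record. Section 10.3 puts disease-related events on those forms, and 10.9 asks for all related events during the study; neither is conditional on having started treatment. Section 8.3.1 provides diaries for home episodes, review of diaries and telephone logs at each visit, and a three-month search of hospital databases, which at the first visit reaches back roughly to randomisation. Table 1 schedules assessment of both events at visits timed from randomisation. Routine forms record every admission.

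The gap may also be short. Both arms share the 14-day limit, consent is ideally within five days of diagnosis (6.1), baseline assessments precede randomisation (6.3), and Roche pumps are issued from site stock at randomisation (7.4). Opening at treatment also follows the adverse event definition in 10.1.1, and the analysis plan, not shown here, may define the counting window.

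Much of this stands. A reader might infer from 10.6 that no event in a non-starter is reportable for the whole year. Sections 10.3 and 10.9 do not support that: the text is inconsistent, not uniformly exclusionary. A reader might also infer that the omission favours CSII. That needs later or more often missed pump starts, and the protocol gives no start times by arm.

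The reply does not remove the inconsistency. Section 8.3.1 names 10.6 as the route, and 10.6 is restrictive. Sites that follow 10.6 and sites that follow 10.9 would record different things. An analysis plan can choose how to count, but it cannot dependably recover events that sites were told not to report.

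**Conclusion.** The point holds as an inconsistency with a risk of bias, not as a demonstrated bias. Taken literally, 10.6 gives two safety endpoints a start set by treatment received, contrary to 8.1, 9.6 and 11.2 and narrower than 10.3 and 10.9.

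For children who start on time the gap is at most about 14 days, or up to about 4% of a year's events at a constant rate. The larger figures need an assumed early rate two to five times the later one, with nothing recovered elsewhere. Non-starters would add to this, but their number is not known. Neither direction nor size can be established from the protocol. The change is still worth making, because it removes the risk at very little cost.

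**What to change.** In both parts of section 10.6, open the reporting window for severe hypoglycaemia and diabetic ketoacidosis at randomisation, for every randomised child whether or not the allocated treatment was started. This brings 10.6 into line with 8.1, 10.3 and 10.9. State that both endpoints are counted from randomisation, so that ketoacidosis present at diagnosis, before randomisation, is not an endpoint event. The relatedness wording needs no change, since 10.6 already covers events related to the disease under study.

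The cost is two sentences, matching CRF guidance, and a few extra related-AE forms from the first two weeks. There are no new visits and clinical management is unaffected.
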